	**Secondary outcomes**																			
		Child attention				✓						✓						✓		
		Child behavior				✓						✓						✓		
		Parenting				✓						✓						✓		
		Parental stress				✓						✓						✓		
	**Exploratory outcomes**																			
		Child health				✓						✓						✓		
	**Moderators and selected confounding variables**																			
		Sex of the child	✓																	
		Socioeconomic situation	✓																	
		Cognitive abilities of the caregiver				✓														
	**Qualitative assessments**																			
		Interviews with caregivers				✓						✓						✓		
		Focus groups with caregivers										✓								
		Focus groups with DBS^g^ and PA^h^ facilitators										✓								

^a^T0: allocation and enrollment.

^b^T1: baseline.

^c^II: intensive intervention.

^d^T2: post–intensive intervention assessment.

^e^EI: extensive intervention.

^f^T3: post–extensive intervention assessment.

^g^DBS: dialogic book-sharing.

^h^PA: playful activity.

**Table 4 table4:** Primary and secondary outcome measures.

Outcomes			Measures
**Primary outcomes**			
	Child language	Receptive and expressive language: MacArthur-Bates Communication Development Inventory (short-form version; adapted) Receptive language: Peabody Picture Vocabulary Test (adapted) Expressive language: Expressive One Word Picture Vocabulary Test (adapted)	
	Parental sensitivity and parent-child reciprocity	Parental sensitivity and parent-child reciprocity: directly observed book-sharing task rated with the Murray Global Rating Scale	
**Secondary outcomes**			
	Child attention	Early Child Vigilance Task	
	Child behavior	Prosocial behavior: help task Prosocial behavior: Strengths and Difficulties Questionnaire (prosocial subscale) Behavior: Strengths and Difficulties Questionnaire; total difficulties score	
	Parenting	Parental engagement with child: frequency of engagement in joint play with child, self-recorded in diaries Parenting practices: Parenting Styles and Dimensions Questionnaire (connection, physical coercion, and verbal hostility dimensions) Parenting efficacy: Parenting Self-Efficacy questionnaire (TOPSEa; selected questions)	
	Parental stress	Parental Stress Scale	
**Exploratory outcomes**			
	Child health	Incidence of diarrhea Wasting Stunting Underweight	

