#### Exploratory Outcomes (Child Health)

To assess child health, caregivers reported whether the child experienced diarrhea in the past 2 weeks. In addition, children’s height and weight were measured to check their nutritional status (stunting, wasting, and underweight).

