### Data Analysis

#### Statistical Analysis Plan

All data will be analyzed by an independent statistician using R (R Foundation for Statistical Computing) or Stata (StataCorp LLC). Fidelity will first be described with standard descriptive statistics. Hypothesis tests will be 2-sided with α of .05, and effect-size statistics will be reported to indicate the magnitude of any intervention effects.

Outcomes are classified a priori as primary, secondary, or exploratory. For the primary outcomes, we will use the Holm-Bonferroni method to adjust *P* values. Secondary and exploratory outcomes will be interpreted as hypothesis generating; the Benjamini-Hochberg procedure will be applied for their significance evaluation.

The primary and secondary outcome analyses will follow the intention-to-treat principle.

Linear mixed models or, where appropriate, analyses of covariance will evaluate intervention effects at both the intensive and extensive postintervention phases, always adjusting for baseline outcome scores. Because participants are clustered, a random effect will be included, and fixed-effect estimates will be compared with intercluster variability. Before modeling, every numerical predictor will be mean centered and standardized (*z* scores); interaction terms will be created as products of these centered variables. Candidate covariates and moderators (child age, dwelling place, child sex, socioeconomic situation, and parental cognitive abilities as indexed by education) will be retained only if they are significant or if removing them markedly alters other parameter estimates.

Although the intention-to-treat approach is the primary approach, a complementary per-protocol analysis will be performed to clarify whether any lack of impact arises from deficiencies in the intervention itself or from participants’ incomplete exposure to it.

Multicollinearity among predictors will be assessed using variance inflation factors, with appropriate mitigation strategies applied where necessary.

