#### Statistical Power

The required sample size was calculated according to accepted mathematical principles (48,49].

The sample size in each of the 3 arms of the study was computed using the following formula:

where α of .05 is the significance level, ...1–β (.80) is the power of the test, and *z*_1–α/4_ (2.24) and z_1–β_ (0.84) are quantiles of the standard normal distribution. The significance level α of .05 is divided by 4—the number of comparisons performed while primary hypotheses are tested (in fact, this is the so-called Bonferroni correction). All tests have 1-sided alternatives. On the basis of the previous meta-analytic studies [52,53], power is guaranteed for the effect size of 0.5. Finally, *DE* is the so-called design effect. It takes into account the clustered nature of data and is computed using the following formula:

DE = 1 + ([cv2 + 1]m –1)ICC

where the *m* value of 3 is the expected average cluster size, *ICC* is the intracluster correlation coefficient, and *cv* is the coefficient of variation of the cluster size. We set the *IC*C at 0.05—more than twice the commonly reported value of approximately 0.02 in comparable parenting studies. This higher value inflates the design effect and, in turn, the required sample size, providing a buffer that preserves statistical power. The value of *cv*^2^=2/9 was used, corresponding to a discrete uniform distribution of cluster sizes from 1 to 5. This range reflects both the settlement layout and our clustering procedure, which aimed to retain as many eligible households as possible while keeping clusters compact (refer to the Eligibility, Recruitment, and Randomization section). Substituting these values into the formula mentioned earlier, one obtains a *DE* of 1.13.

Taking into account a potential attrition rate of up to 15%, the required sample size of each arm is 100. Observations with missing values of the outcome variable will be excluded from the analysis that deals with the given outcome but could still be included in other analyses. Missing values in covariates will be substituted by their regression estimates based on other covariates. The impact of the substitution will be discussed by comparing the current estimates with those obtained if the observations with missing values were excluded.

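### Stunting, wasting and underweight are listed only as categories although height and weight are measured at every round; adding the growth z-scores as analysed exploratory outcomes would avoid a loss of at least 36% of the information

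*Protocol article*

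**What the plan says.** Table 4 of the protocol article lists four exploratory child-health measures: "Incidence of diarrhea Wasting Stunting Underweight". The section Exploratory Outcomes (Child Health) explains where they come from. For diarrhea, "caregivers reported whether the child experienced diarrhea in the past 2 weeks". For growth, the children's "height and weight were measured to check their nutritional status (stunting, wasting, and underweight". No z-score is named as an outcome, and no cut-off or expected prevalence is given. The overview of Study Assessments states that the same procedure, including height and weight, was repeated at all three rounds, and Table 3 marks child health at each of them.

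The section Statistical Analysis Plan describes the modelling in general terms: "Linear mixed models or, where appropriate, analyses of covariance will evaluate intervention effects", "always adjusting for baseline outcome scores". No model for binary outcomes is named. On status, "Secondary and exploratory outcomes will be interpreted as hypothesis generating", with the Benjamini-Hochberg procedure applied to their significance tests.

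**The concern.** Child health is one of the three impact domains in the Objective and the Aims, and the exploratory outcomes will be significance-tested, not only described. For growth, the trial holds continuous measurements on every assessed child, including a baseline value. The listed outcomes reduce each of these to one of two categories. Two children just either side of a threshold then count as different, while a child far below it and one just below it count as the same. A real but modest shift in growth could easily go unseen, and a null result could be misread as no effect on growth.

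There is also a mismatch of form. The modelling sentence, with its adjustment for baseline scores, suits continuous z-scores directly. It does not suit yes/no outcomes as naturally, and diarrhea is yes/no however it is handled.

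**Working it through.** **Related figures in the plan.** The article gives no power, prevalence or precision for child health. Its design effect, used in step 3 below, reproduces: 1 + ((2/9 + 1) × 3 − 1) × 0.05 = 1.133, stated as 1.13. The stated 100 per arm also reproduces to within rounding. The formula is not legible in the text at hand, so the standard two-mean form is assumed: 2 × ((2.24 + 0.84)/0.5)² ≈ 76.0 with unrounded quantiles; × 1.133 = 86.2; then 101.4 if divided by 0.85, or 99.1 if multiplied by 1.15. That calculation serves the primary outcomes only.

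**Step 1. Information kept after a cut.** Assumptions: the underlying score is normal, the intervention causes a small pure shift, and each category is formed by cutting that score at a point leaving a proportion p below it. The efficiency of the category relative to the continuous score is φ(z_p)² / [p(1 − p)], where φ is the standard normal density and z_p the p-quantile. The share lost is one minus this.

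| Assumed prevalence p | Relative efficiency | Information lost | Sample-size multiple for equal precision |
|---|---|---|---|
| 5% | 0.224 | 78% | 4.47 |
| 15% | 0.426 | 57% | 2.35 |
| 30% | 0.576 | 42% | 1.74 |
| 50% | 0.637 | 36% | 1.57 |

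For example, at 5%: φ(−1.645)² / (0.05 × 0.95) = 0.0106/0.0475 = 0.224.

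**Step 2. Lower bound.** Efficiency is highest at p = 50%, where it equals 2/π = 0.637. The loss is therefore at least 36% whatever the true prevalence.

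**Step 3. Illustration in terms of power.** The article includes 443 caregivers in three arms and allows for up to 15% attrition. The number per arm is 443/3 × 0.85 = 125.5, and the effective number is 125.5/1.133 = 110.75. This carries the design effect over to child health, which is an assumption. Take an assumed shift of 0.3 SD, a two-sided 0.05 test and no baseline adjustment.

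- Continuous score: Φ(0.3 × √(110.75/2) − 1.96) = Φ(2.23 − 1.96) = 61%.
- Category, by the two-proportion normal approximation: 15% power at 5% prevalence (falling to 2.6%), 27% at 15% (falling to 9.1%) and 37% at 30% (falling to 20.5%).

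At an assumed 5% prevalence, about 125.5 × 0.05 = 6.3 affected children would be expected per arm.

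**Step 4. Is the continuous outcome available?** Height and weight are taken at all three rounds. Eligibility rests on date of birth, and child sex is recorded (Table 3). Stunting and underweight are themselves age-referenced, so age is needed for the listed categories anyway. No new data are required.

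**Step 5. Diarrhea.** The source item is a yes/no report over 2 weeks, so no score has been cut and steps 1 to 3 do not apply. Whether a child had diarrhea in a 2-week window is a period prevalence; Table 4 calls it incidence.

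**The case against.** The strongest objection is that this is a condensed article. Anthropometric scoring and the model for a binary exploratory outcome are details that a fuller plan often holds. This stands in part: the lack of a named binary model is not an error in itself. A reader might infer that the plan throws away the continuous values and fits a Gaussian model to rare 0/1 data. The article does not say so. Its modelling sentence is general and does not mention child health, and nothing in the article shows that the outcomes are rare. What the article does fix is the form of the growth outcomes, and a fuller plan that analysed z-scores would be adding to Table 4.

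Second, a linear model on a 0/1 outcome in a randomised comparison still estimates a risk difference, and fitted values outside 0 to 1 do not invalidate it. That stands, and no harm from such a model is claimed here. A mixed logistic model could itself be unstable with few events, since clusters hold only 1 to 5 households.

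Third, a shift in mean z-score and a change in the proportion below a threshold are different questions, and the article states that data collection ended in September 2024. Replacing or demoting listed outcomes at this stage would be hard to defend. This stands, and it is why the z-scores should be added and the categories kept.

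Fourth, the outcomes are hypothesis generating and outside the sample-size basis. That also stands and limits the severity.

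**Conclusion.** The point holds as a cheap improvement of low severity. Three of the four child-health outcomes are listed only as categories although their continuous source is measured at every round. Under normality and a small location shift, the cut loses at least 36% of the information. The larger losses depend on prevalences that the article does not give. The power figures are illustrations that further assume a 0.3 SD shift and the planning design effect.

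Two stronger readings should be avoided. The percentages are shares of the information that the cut discards, not shares of that loss that could be regained; under the stated assumptions the continuous score avoids the whole loss. And the argument does not cover diarrhea, where the only issues are the model and the label. No confirmatory conclusion of the trial is affected.

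**What to change.** 1. Add height-for-age, weight-for-height and weight-for-age z-scores to Table 4 as analysed exploratory growth outcomes, using the planned mixed model with the baseline z-score as covariate and the cluster random effect.
2. Keep stunting, wasting and underweight as listed and report them alongside the z-scores.
3. Date the addition and state in the report that it was made after data collection was complete.
4. Name a binary model for diarrhea that allows for clustering. With such small clusters, a marginal logistic model with cluster-robust standard errors is an option if a random-intercept model is unstable. Call the outcome 2-week prevalence.

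The cost is wording in the analysis plan and no new data. There are two small downsides: z-score differences are less familiar to readers than percentages, and three more exploratory outcomes enter the Benjamini-Hochberg family.

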**Moderators and selected confounding variables**			
	Sex of the child	Child's sex (male or female)	
	Socioeconomic situation of families	Asset index	
	Parental cognitive abilities	Vienna Matrices Test	

^a^TOPSE: Tool to Measure Parenting Self-Efficacy.

#### Primary Outcomes

##### Child Language

Child language was assessed using a combination of direct child assessment and caregiver-reported measures. Caregivers reported on their children’s expressive and receptive language levels using the MacArthur-Bates Communication Development Inventory [34]. For this study, a short version with 55 words was used.

Two assessment tools were used to complement the MacArthur-Bates Communication Development Inventory with direct measures of child language. Language comprehension (receptive language) of all children was measured using an adapted version of the Peabody Picture Vocabulary Test [35] during which the child was shown pictures of 80 items in groups of 4. The child was asked to point to 1 named item among the 4 (eg, “Where is the goat?”), with the number of correct responses recorded.

Expressive language was only assessed in the group of children aged between 30 and 45 months, using the adapted Expressive One Word Picture Vocabulary Test [36]. The child was asked to say the name of the item shown on a screen. In total, 20 pictures were shown, and the number of correct responses was recorded.

All these instruments have been used in previous evaluations of book-sharing programs in African contexts in the same form as in our study [15,21-23,37]. To reflect the vocabulary to which local children in our study setting are typically exposed, we only adapted the set of words in each test based on numerous consultations. The instruments were piloted with 10 caregiver-child dyads.

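### The 80% power statement does not cover the expressive picture-vocabulary test, a primary measure given only to the older age band

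*Protocol article*

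**What the plan says.** Three places in the protocol article bear on this.

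- Table 4, under primary outcomes and child language, includes "Expressive language: Expressive One Word Picture Vocabulary Test (adapted" alongside the MacArthur-Bates inventory (caregiver report, receptive and expressive) and the adapted Peabody test (receptive).
- The Child Language section restricts the picture-naming test by age: "Expressive language was only assessed in the group of children aged between 30 and 45 months". It says that the Peabody test was given to all children and puts no age limit on the MacArthur-Bates inventory.
- The Statistical Power section derives one sample size per arm. "The significance level α of .05 is divided by 4", the stated power is 0.80, the ICC is 0.05, the mean cluster size is 3, and attrition is allowed for up to 15%. The result is 100 per arm, and the section says that "power is guaranteed for the effect size of 0.5". It makes no exception for a measure taken by part of the sample. It also says that children without a given outcome are left out of that outcome's analysis.

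The two age bands, 15 to 30 months and over 30 to 45 months, are used as a balancing factor in randomization. The number of children in each band is not given.

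**The concern.** The younger band contributes nothing to the analysis of the picture-naming test, so that analysis has fewer children per arm than the power calculation counts. The unqualified power statement does not fit the plan's own description of who takes the test.

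This is the only directly tested measure of expressive language; the other expressive measure is caregiver report. If the result were null, a reader would set it against a claimed 80% power for an effect of 0.5 that was never worked out for the children who took the test.

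**Working it through.** **Inputs from the Statistical Power section.** One-sided alpha 0.05/4 = 0.0125 (z = 2.24), power 0.80 (z = 0.84), standardized effect 0.5, ICC 0.05, m = 3, cv² = 2/9, attrition 15%. From Eligibility, Recruitment, and Randomization: 443 included.

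**Assumptions, because the documents give no figure.** Half the children are in the older band (the bands have equal width; range shown 40–60%). The three arms are equal, so 443/3 = 147.7 per arm. Older children are spread across clusters without regard to cluster.

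**1. Reproduce the plan.**
DE = 1 + ((2/9 + 1) × 3 − 1) × 0.05 = 1.133 (plan: 1.13).
n analysed = 2 × (2.24 + 0.84)² / 0.5² × 1.13 = 75.9 × 1.13 = 85.8.
n enrolled = 85.8 / 0.85 = 100.9, or 85.8 × 1.15 = 98.6. The stated 100 reproduces.
For a full arm of 100 with 15% attrition, power = Φ(0.5 × √(85 / (2 × 1.133)) − 2.241) = 79%. For a full arm of 147.7 it is 93%.

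**2. Design effect in the older band.** If a share p of each cluster takes the test, DE = 1 + 0.05 × p × (11/9 × 3 − 1) = 1 + 0.133p. At p = 0.5 this is 1.067. Keeping the plan's 1.133 gives the lower end of each range below.

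**3. Power for a stand-alone test, half the children older.** Power = Φ(0.5 × √(n / (2 × DE)) − 2.241).

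| Size per arm | Attrition | n analysed | Power, DE 1.133 | Power, DE 1.067 |
|---|---|---|---|---|
| 100 (planned) | 15% | 100 × 0.5 × 0.85 = 42.5 | 47% | 50% |
| 147.7 (enrolled) | 15% | 147.7 × 0.5 × 0.85 = 62.8 | 65% | 68% |
| 147.7 (enrolled) | none | 147.7 × 0.5 = 73.8 | 73% | 76% |

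**4. Sensitivity to the older-band share (40–60%, DE recalculated).** Planned size, 15% attrition: 41–58%. Enrolled size: 58–76% with 15% attrition and 66–83% with none.

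**5. Share needed for 80% power.** At the planned size with 15% attrition, at least 89% of children would have to be older, even with no clustering at all. At the enrolled size, about 61–69% is needed with 15% attrition and 51–58% with none (DE from 1.0 to 1.133).

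**6. Effect detectable with 80% power, half older, 15% attrition, DE 1.067.** (2.241 + 0.842) × √(2 × 1.067 / n) = 0.69 at n = 42.5 and 0.57 at n = 62.8.

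**7. Baseline adjustment.** The analysis plan adjusts for baseline scores, but the sample size takes no credit for this and gives no correlation. Replacing 0.5 by 0.5 / √(1 − r²), with half older, 15% attrition and DE 1.067:

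| r (assumed) | Planned | Enrolled |
|---|---|---|
| 0.5 | 63% | 81% |
| 0.7 | 81% | 94% |

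**8. Sidedness.** The sample-size section says "All tests have 1-sided alternatives", while the analysis section says "Hypothesis tests will be 2-sided with α of .05". With a two-sided 0.0125 (z = 2.498), half older, 15% attrition, DE 1.067 and no baseline credit, power is 40% planned and 58% enrolled.

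**The case against.** The strongest reply is that the article does not define a stand-alone test of this measure. Four comparisons would fit two primary domains (child language; sensitivity and reciprocity) times two comparators, with the picture-naming test as one component of the language domain. That stands as a limit on the figures. But no composite is described, and Table 4 lists the instruments separately. If each is tested on its own, there are more than four comparisons and the correction is stricter than alpha/4. On either reading the power statement needs its scope stated.

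A reader might infer that the trial as run has only about 50% or 68% power for this measure. The documents do not support either as a fact. The 50% belongs to 100 per arm, and 443 were included. The 68% needs an unreported age split, equal arms, the maximum planned attrition and no gain from baseline adjustment. A more favourable split or a strong baseline correlation could remove the shortfall at the enrolled size. At a correlation near 0.7 that holds even at the planned size, though the plan's own calculation does not use it.

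A reader might also infer a sample-size error; there is none, since 100 per arm reproduces. Nor is sharing a Holm family with better-powered tests a harm. Alpha/4 is the strictest step for four tests, and at the last step (one-sided 0.05) 62.8 per arm would give 86%.

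**Conclusion.** The point holds as one of scope. The plan says without qualification that 80% power is assured for an effect of 0.5, and one listed primary measure falls outside the calculation behind that statement.

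At the planned size, on the plan's own inputs, the shortfall is clear for any plausible age split: about 47–50% if half are older, and 41–58% for shares of 40–60% with the design effect recalculated. At the enrolled size a shortfall is likely but conditional: about 65–68% with 15% attrition and 73–76% with none, if half are older. All these figures assume a stand-alone one-sided test at 0.0125 with no credit for baseline adjustment, and the enrolled figures also assume equal arms. The documents do not establish the trial's actual power for this measure, because the band sizes are not reported.

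**What to change.** In the Statistical Power section, limit the 80% power statement to measures taken in all children. Report the number of older-band children per arm; data collection is complete, so the count is known and replaces the assumed half. From those counts, give the picture-naming test its own power or detectable effect, with the alpha, sidedness, ICC, attrition and any baseline correlation stated. If half are older and attrition is 15%, the detectable effect would be about 0.57 at the enrolled size and 0.69 at the planned size. Mark the test in Table 4 as an older-band measure, and say that a null result on it must be read against its own figure.

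The measure should stay primary: reclassifying it after data collection would be a change to the plan, not a clarification. The cost is wording only. Data and analysis are unchanged, and one stated power figure becomes less favourable.
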